### Outcomes

All outcomes are assessed using data collected from the Danish administrative health registries. The outcomes are primarily feasibility-oriented and include:Number of persons contacted by recruitment letterNumber of participants included and randomized to QIV-HD or QIV-SDAgreement between randomization group and administered vaccineAssessment of baseline characteristics according to randomization groupComparison of baseline characteristics between study population and Danish general population aged 65-79 years on October 1, 2021

The study is not powered for assessing clinical endpoints. However, for feasibility assessment purposes, event rates and relative vaccine effectiveness (rVE) will be assessed for the following clinical outcomes:Hospitalization for influenza and/or pneumoniaHospitalization for any respiratory diseaseHospitalization for any cardio-respiratory diseaseHospitalization for any cardiovascular diseaseHospitalization from any causeAll-cause mortalityHospitalization for COVID-19

The clinical outcomes are specified further in Table 4. rVE will be calculated as:

rVE = (1-(C_HD_ /N_HD_)/(C_SD_/N_SD_)) × 100%

Where:

C_HD_: describes the number of endpoints occurring in the QIV-HD arm meeting the endpoint definition

N_HD_: describes the number of participants in the QIV-HD arm

C_SD_: describes the number of endpoints occurring in the QIV-SD arm meeting the endpoint definition

N_SD_: describes the number of participants in the QIV-SD arm

### Assessment of success

Since this is the first trial ever conducted in Denmark to use the setup and design described in this report, the study team found it impossible to devise specific criteria for success with meaningful numerical cutoffs. Significant uncertainties pertaining primarily to the obtainment of approvals for this novel trial design from the Danish authorities and obtaining real-time access to registry data for a drug trial existed, leaving the study team wondering whether it would even be possible to initiate the trial. Due to this, the assessment of success will rely on an overall evaluation of the conduct of the trial including the obtainment of approvals, recruitment rate and success, randomization agreement, and reliability with regards to the registry-based obtainment of baseline characteristics, safety events, and clinical endpoints. This overall evaluation will be used by the study team as part of the decision on whether to progress to a fully powered trial. Any specific issues encountered during this feasibility trial will be addressed in the design of a fully powered trial, in case the study team should decide to progress.

### Safety monitoring

For this trial studying two influenza vaccines already approved for use in the study population, safety monitoring is performed using a pragmatic, registry-based approach. Each subject is assessed for the occurrence of serious adverse events (SAEs) and serious adverse reactions (SARs) at approx. 3 months after vaccination using extracts from the Danish administrative registries. Each episode, primarily deaths and hospitalizations, is assessed for causality, seriousness, and expectedness by a medical doctor based on electronic medical record review. Events are reported to the authorities according to applicable rules and regulations.

### Statistical analysis

Purely descriptive outcomes such as number of persons contacted and recruited will be presented in raw numbers. The proportion of the number of participants recruited compared to the number of persons contacted will be calculated and presented along with a 95% confidence interval. The proportion of participants not receiving the correct intervention will be calculated for each randomization arm and presented along with 95% confidence intervals. In the comparison of baseline characteristics between the study population and the overall Danish general population aged 65–79 years, characteristics will be compared using methods appropriate for each characteristic. Continuous baseline variables will be summarized using means and standard deviations or medians and interquartile ranges. Binary or categorical variables will be compared using frequencies and proportions. Event rates for clinical endpoints will be presented as attack rates and incidence rates with 95% confidence intervals. rVE estimates will be presented along with 95% confidence intervals. *P* values < 0.05 will be considered statistically significant. rVE estimates will be considered statistically significant if the confidence interval does not include 0.

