**Methods:**

The DANFLU-1 trial (NCT05048589) is a pragmatic, open-label, active-controlled randomized trial randomizing Danish citizens aged 65–79 years to either high-dose quadrivalent influenza vaccine or standard-dose quadrivalent influenza vaccine. The study utilizes the infrastructure of a private vaccination provider (Danske Lægers Vaccinations Service) for recruitment, inclusion, randomization, and vaccination. All collection of baseline and follow-up data including safety monitoring is performed centrally by the Department of Cardiology at Herlev and Gentofte Hospital, Copenhagen, Denmark using the Danish nationwide health registries. The study aims to include 40,000 participants during the 2021/2022 influenza season. The primary endpoints address feasibility and include the number of participants enrolled, randomization balance, and representativeness compared to the Danish general population. Relative vaccine effectiveness will also be assessed, however, this feasibility study is not powered for clinical outcomes and may be affected by the COVID-19 pandemic.

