### Study population and sample size

Due to the pragmatic nature of the study, the only inclusion criteria are that the participants are aged 65–79 years and that the informed consent form has been signed and dated. The only exclusion criterion is allergy/hypersensibility toward the vaccines used in the study. Potential contraindications (fever etc.) are evaluated as part of routine practice on the day of vaccination.

Potential participants will be recruited by sending invitation letters to citizens vaccinated in prior seasons as recorded in an existing DLVS database. In addition, broader website-based advertising is also utilized. The projected sample size of 40,000 was chosen to, in the opinion of the study team, place vaccine delivery and vaccination program infrastructure and systems under sufficient pressure to inform the feasibility and planning of a future fully powered study. A preliminary sample size calculation yielded a required study population of 208,675 participants for a fully powered study under the assumptions of a true relative vaccine effectiveness (rVE) of QIV-HD to QIV-SD of 15%, an overall attack rate of hospitalization for influenza and/or pneumonia of 0.86% in the QIV-SD group, alpha of 0.05, and power of 0.90. Thus, this present study is not powered for the assessment of any clinical endpoints.

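### The recruitment proportion, as written, sets all participants against persons sent a letter, although recruitment also runs through website advertising; if anyone enrolled without a letter, it is not a proportion and its 95% confidence interval has no valid target.

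*Protocol article*

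**What the plan says.** The Statistical analysis section of the protocol article commits to a specific ratio: "The proportion of the number of participants recruited compared to the number of persons contacted will be calculated". A 95% interval is to accompany it. The section does not limit the numerator by recruitment route, and it does not define contact.

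The Outcomes section supplies the only two counts that fit. One is the number of people reached by a recruitment letter. The other is everybody enrolled and randomized to either vaccine, whatever brought them in. No count of people reached through a website is listed.

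The section Study population and sample size describes two routes. The first: "Potential participants will be recruited by sending invitation letters to citizens vaccinated in prior seasons as recorded in an existing DLVS database". The second: "In addition, broader website-based advertising is also utilized".

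On use, the section Assessment of success includes "recruitment rate and success, randomization agreement, and reliability with regards to the registry-based obtainment of baseline characteristics" among the matters to be weighed in deciding whether to go on to a fully powered trial, without numerical thresholds. The abstract says: "The primary endpoints address feasibility and include the number of participants enrolled, randomization balance, and representativeness compared to the Danish general population". The recruitment proportion is not named there.

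**The concern.** A confidence interval for a proportion presupposes that each unit in the denominator either is or is not a success, so that the numerator is a subset of the denominator. Here the denominator appears to be people sent a letter, while the numerator appears to be all participants. Someone who enrolled after seeing the website, and who was not on the mailing list, adds to the top and not to the bottom.

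What is at stake is how the feasibility result is read. A figure labelled as a proportion recruited out of those contacted will naturally be taken as the response to an invitation letter. Any web-only participants push it above that response, never below. With counts of this size the interval will be very narrow, so it would give an impression of precision around a quantity that it does not estimate. Letter response and advertising yield need not grow together in a larger trial, and the pooled figure cannot separate them.

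**Working it through.** The article states no recruitment proportion, no number of letters and no split of participants by route, so there is no published figure to reproduce. The check is an algebraic comparison with an illustration.

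**Inputs**
- N = 40,000 participants, from the abstract: "The study aims to include 40,000 participants during the 2021/2022 influenza season".
- L = letters sent. Not given; assumed 100,000, 200,000 or 400,000.
- w = share of participants not sent a letter. Not given; assumed 0 to 20%.

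**Step 1: the two quantities**
- Ratio as written: R = N / L
- Response to letters: p = N(1 - w) / L
- R / p = 1 / (1 - w), whatever L is.

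| w (assumed) | 1/(1-w) | Overstatement if read as letter response |
|---|---|---|
| 0 | 1.00 | none |
| 5% | 1/0.95 = 1.05 | 5% |
| 10% | 1/0.90 = 1.11 | 11% |
| 20% | 1/0.80 = 1.25 | 25% |

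**Step 2: the error against the width of the interval**

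The Wald half-width is h = 1.96 × √(R(1 - R)/L), and the error is R - p = wR. The error exceeds h once w > h/R.

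| L (assumed) | R | h | w at which error = h | Error/h at w = 5% | Error/h at w = 10% |
|---|---|---|---|---|---|
| 100,000 | 40% | 0.30 points | 0.76% | 6.6 | 13.2 |
| 200,000 | 20% | 0.18 points | 0.88% | 5.7 | 11.4 |
| 400,000 | 10% | 0.09 points | 0.93% | 5.4 | 10.8 |

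For example, with L = 200,000 the reported figure would be 20.0% (19.8% to 20.2%). The response to letters would be 20.0% × 0.95 = 19.0% at w = 5%, and 20.0% × 0.90 = 18.0% at w = 10%. Both lie well outside the interval. Across these letter counts, a web-only share of about 0.8% to 0.9% is enough for the interval to miss the letter response.

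**Step 3: is it a proportion at all?**

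Nothing in the definition keeps R below 1. With L = 30,000 (assumed, to make the point), R = 40,000/30,000 = 1.33, for which the binomial formula has no meaning. This is an illustration of the definition and not a forecast.

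**The case against.** The strongest reply is that the mismatch is assembled from three sections. The Statistical analysis section does not repeat that contact means a letter, nor does it say that web recruits are counted. A numerator confined to people who were contacted would be compatible with its wording, and the full protocol or analysis plan may define it so. That is fair as far as it goes. But the article does more than omit a detail. It fixes the ratio and the interval, lists only one count of contacts and one unrestricted count of participants, and describes a second recruitment route. The plain reading of those three together is the faulty one.

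It can also be said that the two counts will be given as they stand and that both routes are disclosed, so a reader can see what was divided. This limits the harm, but the split by route is not promised, and without it the letter response cannot be recovered.

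Three stronger readings are tempting and are not supported:
- **That the rate is overstated.** This depends on w, which the documents do not give. A person who was sent a letter and also saw the website belongs in the numerator.
- **That this is the headline feasibility result.** The abstract names enrolment, randomization balance and representativeness. The recruitment rate mentioned under Assessment of success is not defined as this ratio, though it plausibly draws on it.
- **That a trial of the 208,675 participants in the preliminary calculation, planned on this figure, would send too few letters (20% too few at w = 20%).** That holds only if the later trial recruits by letter alone. If the same mix of letters and website were repeated with the same relative yield, total enrolment per letter would be a serviceable planning figure.

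**Conclusion.** The concern holds conditionally. On the plain reading of the three sections, if any participant was not sent a letter, the planned figure is not a binomial proportion and its 95% confidence interval has no valid target. Taken as response to letters, it is then too high by a factor 1/(1-w). The direction and the formula are certain under that reading; the size is not, because w and the number of letters are assumptions here.

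Severity is minor to moderate. The figure is descriptive, no numerical cutoff rests on it, and the randomized comparison, vaccine agreement, baseline comparisons and safety assessment are untouched. It merits correction because recruitment informs the decision on a fully powered trial and the remedy is simple.

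**What to change.** In the Statistical analysis section, define the recruitment proportion as participants who were sent a recruitment letter divided by all persons sent one, with its 95% confidence interval. A participant who was sent a letter and also saw the website stays in the numerator. Report participants not sent a letter separately, as a count and as a share of all participants. If total enrolment per letter is also wanted, show it, label it a ratio, and attach no binomial interval.

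The classification needs enrolled participants to be matched to the vaccination provider's mailing list. The article says that the letters are drawn from the provider's database and that the provider records social security number and name at enrolment. It does not say which identifiers the mailing list carries, so the match should use whatever identifier is held.

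The cost is a sentence or two of text, a small matching task and possibly a lower reported rate. Nothing in the design or conduct of the trial changes.

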### Ethical statement

The study complies with the standards of the CONSORT statement and the principles of the Declaration of Helsinki and undergoes monitoring according to the International Conference on Harmonization guidelines for Good Clinical Practice. The study has been approved by the regional research ethics committee (H-21035316), the Danish Medicines Agency (2021-003170-31), and the data authority in the Capital Region of Denmark (P-2021-407). The study is registered in the European Union Clinical Trials Register (EudraCT no. 2021-003170-31) and on Clinicaltrials.gov (NCT05048589).

Both negative, positive, and inconclusive results will be submitted for publication in peer-reviewed journals. Authorship criteria will be based on Recommendations for the Conduct, Reporting, Editing, and Publication of Scholarly Work in Medical Journals by The International Committee of Medical Journal Editors. The results of the study will be published on Clinicaltrials.gov and in the EudraCT database.

## Discussion

To our knowledge, this is the largest study ever conducted in Denmark combining data collection from the renowned Danish nationwide administrative health registries with key elements from a gold standard RCT design. This feasibility study will provide valuable insight, especially for a potential future fully powered QIV-HD vs. QIV-SD trial, but will also provide operational and regulatory lessons for trials of other interventions conducted within the Danish health system.

The implementation of registry-collected data from real-world clinical events and procedures into randomized clinical trials provides trial sponsors and funders with a powerful tool to increase the scope and reduce the costs of large-scale trials. Event data can be passively collected instead of requiring active review of medical records or contact with study participants, enabling capture of a greater number of rare or difficult-to-ascertain endpoints, which may otherwise have been infeasible. This could in turn reduce total drug and vaccine development cost, benefitting patients and health systems due to a potential lower cost of the market-ready drug. The approach allows for robust measurement of effectiveness across a large number of potential indications and could provide increased confidence in health economic analyses, treatment guidelines, and clinical practice decisions.

Danish registry data has previously primarily been used for observational studies [22]. A reassuring finding of these studies is the minimal risk of loss-to-follow up due to the universal nature of the Danish healthcare system, a theoretical risk of pragmatic studies in which participants are not actively followed over time. Observing outcomes through the public health system lowers costs and complexity, but, more importantly, improves generalizability by allowing streamlined conduct of nationwide clinical trials without the need to coordinate across different health service providers and allows almost any citizen partaking in annual influenza vaccination to be included in a clinical study. This feature increases the likelihood of the findings being generalizable to real-world clinical practice and eases the complexity of interpreting or extrapolating results into specific population groups who may be at heightened risk.

Assessment of clinical endpoints using registry data is dependent on reliable coding and classification of hospital contacts by treating clinicians, and while a large proportion of diagnoses in the Danish registries are highly validated with high positive predictive values [13, 23–26], this might introduce the risk of underreporting when compared with laboratory-confirmed endpoints following active surveillance from regular clinical trials. Our study includes cardiovascular endpoints for which adjudication is commonplace, but the value of this approach has recently been questioned. A post-hoc analysis from the ASCEND trial assessing aspirin and/or ω-fatty acids for prevention of cardiovascular events in people with diabetes showed a strong agreement between routinely collected data and adjudicated follow-up for serious vascular events, and using routine data yielded similar effect sizes compared with adjudicated follow-up [27]. Additionally, in reports from the SHIFT [28] and PARADISE-MI [29] heart failure medication trials, it has been shown that adjudication did not have a meaningful impact on the studies’ effect estimates when compared to “raw” investigator-reported events. Additionally, using registry-based endpoints might even improve external validity of the study results [30].

A potential limitation of this registry-based approach is the lack of active surveillance and systematic laboratory confirmation corresponding to the primary study endpoint [31]. These features of classical efficacy clinical trials guarantee a relatively high incidence rate of specific events corresponding to regulatory requirements [32, 33]. Pragmatic, registry-based studies are therefore currently most relevant for post-licensure assessment.

This study is conducted as an open-label trial reducing the complexity and documentation demands related to handling of the vaccines at the vaccination sites. This will not impact the feasibility-oriented endpoints and would be expected to introduce only minimal bias in a potential future study evaluating registry-based hard clinical endpoints such as deaths and hospitalizations with prespecified definitions, especially in a trial comparing two active treatments without a placebo arm.

Based on extensive experience with both high-dose and standard-dose influenza vaccines from clinical practice and large-scale phase 3 trials [9, 34], and many years of use of both vaccine types in routine practice, it was agreed with the authorities that only the collection of SAEs, specifically deaths and hospitalizations, would be required. This further strengthens the case for the registry-based design since all deaths and hospitalizations in the Danish public health system can easily be passively collected from registry extracts, once again reducing the cost and complexity associated with the trial.

## Conclusions

The DANFLU-1 study is investigating the feasibility of conducting a large-scale pragmatic clinical trial in Denmark utilizing existing infrastructure for recruitment, randomization, and vaccination and the Danish nationwide registries for collection of baseline and follow-up data. This study will provide valuable insight, especially for potential future fully powered vaccine trials, but also for trials wishing to investigate other interventions.

## Data Availability

Baseline and endpoint data from this trial stems from Danish administrative health registries, which are subject to Danish legislation and can only be made available to a third party under certain conditions. Please contact the corresponding author in case of any inquiries.

## Abbreviations

ATC: Anatomic therapeutic chemical
CIRL: Cardiovascular Non-Invasive Imaging Research Laboratory
DLVS: Danske Lægers Vaccination Service
HA: Hemagglutinin
HD: High-dose
ICD: International Classification of Diseases
QIV-HD: High-dose quadrivalent influenza vaccine
QIV-SD: Standard-dose quadrivalent influenza vaccine
RCT: Randomized controlled trial
rVE: Relative vaccine effectiveness
SAE: Serious adverse event
SAR: Serious adverse reaction
SD: Standard-dose
SSI: Statens Serum Institut
